### Data collection, management and analysis

***Data collection*.** Patients will be in the trial for a maximum of 24 months or until death (see study schedule in
Table 2). Generic quality of life is followed every 3
^rd^ month using EQ-5D 3L. Quality of life will be monitored until progression, death or 24 months post-inclusion
^24,
27^.

MRI scanning will be performed at a minimum of every 3
^rd^ month. MRI assessment may continue up to 24 months post-inclusion and this should be implemented also after documented progression in the DSF-Cu group, as long as the patient continues on only DSF-Cu, or in combination with another established rescue therapy such as surgery, radiation therapy or other alkylating chemotherapy. Consequently, MRI controls are indicated and should be continued as long as tumor targeted therapy is administered (both in control and intervention group). The RANO criteria is used in MRI assessment and for evaluation of progression
^28^.

After withdrawal of tumor target therapy no additional follow-up (including MRI) is planned within the context of this study, in order to minimize patient burden in the end of life setting. Safety assessment are according to the Common Terminology Criteria for Adverse Events (CTCAE) version 4.0
^29^. Survival is followed until death or 24 months post-inclusion.

***Data management*.** Data will be recorded in the web-based eCRFs (WebCRF 3.0) at The Unit for Applied Clinical Research at the NTNU. All data will be entered in the WebCRF 3.0 at the local study site. All electronic patient information is handled using a study participation number that is not logically connected to any personal data. It is possible to manually “decode” back to personal data using a name list stored securely at the respective study sites.

All data entered into the WebCRF are stored at two separate servers at NTNU. These servers are protected by the general firewall at the university and then by another firewall dedicated to protect clinical research data. The server that stores the data is not the same server as the one in contact with the Internet. There are several further safety measures not to be exposed. There are backups taken every 24-hour throughout the years. The responsibility for this system lies with the Unit for Applied Clinical Research at NTNU.

***Statistical methods*.** All outcomes will be analyzed according to the intention to treat principle unless otherwise specified in post-hoc analyses. This is an open label trial, however the statistician performing analyses will be blinded for treatment assignment. Also, an investigator blinded for treatment allocation will perform the assessment of radiological end-points.

The 6-month survival (i.e primary end-point) will be assessed with 2x2 tables and analyzed with chi-square test. This analysis will be performed 6-months after last patient inclusion. Concerning the primary end-point we do not expect any missing data.

Concerning the secondary outcomes they will be evaluated as follows:

 Actual survival data at 24 months post-inclusion will be analyzed similar to the primary end-point. Overall survival analyses will be analyzed using Kaplan-Meier plot and tested with log-rank test. This analysis will be performed at 6 months after the last patient inclusion together with the assessment of primary outcome. Also, this will be analyzed in a longer-term follow-up study (24 months post-inclusion). Overall progression free survival will be analyzed with Kaplan-Meier plot and tested with log-rank test. This analysis will also be performed at 6 months and at 24 months after the last patient inclusion. The assessment of progression will be done in accordance with the latest RANO criteria by the local investigator. Actual progression free survival analyses at 6 and 24 months after the last patient inclusion. The assessment of progression will be done in accordance with the latest RANO criteria by the local investigator and analyzed similar to the primary end-point. Comparison of general health related quality of life at 6 and 24 months after last included patients. We will use an area under the curve approach (i.e. cumulative quality of life)
^27^. Semiautomatic segmentation of contrast-enhancing tumor volume assessed at baseline and first MRI control to assess growth dynamics. The data will be analyzed with independent samples t-test or Mann-Whitney U test, based on data distribution. Safety assessment with comparing proportion of a composite of grade 3, 4 and 5 toxicities according to the common terminology Criteria for Adverse Events (CTCAE).

We stratify only for study center, however important baseline variables like repeated surgery, time since primary treatment, age, functional status, lomustine versus temozolomide treatment, and biomarker status from initial surgery if available (IDH and MGMT) will be registered and adjusted for in post-hoc exploratory analyses. Also, we will explore outcomes in post-hoc as treated analyses if non-compliance to treatment protocol becomes apparent.

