The administration of DSF and nutritional copper supplement is scheduled to start concomitant with alkylating chemotherapeutic treatment. Patients will take DSF (Antabus
^®^) as a once daily oral dose of 400 mg, based on the known toxicity profile
^9^. In case of intolerance, dose reduction to 200 mg per day is allowed. Copper supplementation will be administered separately from DSF with DSF administration in the evening. Copper nutritional supplement will correspond to 2.5 mg of elementary copper, which is not considered a safety concern
^23^. Adherence to treatment will be assessed at each control with a reminder, self-reporting of drug intake and drug tablet count of remaining DSF. The only surveillance of nutritional copper intake is by self-reporting.

Before study closure no crossover from the control group to DSF-Cu is allowed.

The intervention should continue also after change of chemotherapy, or during temporary chemotherapy withdrawal due to reached maximal cumulative dose or side effects from chemotherapy.

Patients are to discontinue permanently the treatment with DSF-Cu for any of the following reasons:

 Unacceptable adverse effect(s) as judged by the treating doctor. No longer indication for tumor targeted therapy. The patient wishes to withdraw from treatment. If patients develop conditions that contribute to excess risk as judged by the treating physician.

Other experimental therapy, including compassionate use programs, are not allowed in either treatment group as long as the patient is in the trial and receives the assigned treatment.

***Outcomes*.** The primary end-point of the study is survival assessed at 6 months post-randomization.

Secondary end-points are:

 Overall survival from date of randomization. Median progression free survival. 6 and 12 month progression free survival. Health-related generic quality of life
^24^. Volumetric growth rate assessed from baseline MRI to first follow-up MRI scan
^25^. Safety assessment (toxicities).

***Participant timeline*.** To reduce patient burden, timing of data collection after randomization is scheduled according to choice of chemotherapy regimen, where patients that receive temozolomide usually are assessed every 4
^th^ week while patients treated with PCV/lomustine are assessed every 6
^th^ week. Consequently, this may lead to four additional observations in the temozolomide group compared with the lomustine/PCV group. The more detailed clinical control and MRI assessment every 3

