^rd^ month is independent of chemotherapy regimen. The primary endpoint will not be affected by the differences in timing of assessments during the trial.

Finally, hematological status and liver function will be monitored as long as patients are on active treatment every 4–6 weeks, once again depending on the chemotherapeutic protocol (
Table 2).

**Table 2. T2:** Schematic view of study schedule with timing and content of study visits.

Visit	Screening	Monthly	Every 3 months
Month *	0	1,2,4,5,7,8,10,11	3,6,9,12,15,18,21,24
Eligibility	X		
Informed consent	X		
Alcohol screen **	X		X
KPS	X	X	X
Demographics	X		
Pregnancy test	X		
Medical history	X		
Euroqol-5D 3L	X		X
Toxicity/AE/SAE/SAR and SUSAR		X	X
Compliance		X	X
Discontinuation		X	X
Consider drug interactions	X		X
MRI Scan	X		X
Blood samples:			
Hematological and liver monitoring ***	X	X	X

AE denotes adverse event, SAE; serious adverse event, SAR; serious adverse reaction SUSAR; suspected unexpected serious adverse reaction, MRI; magnetic resonance imaging, KPS; Karnofsky Performance Status *The interval for patients treated with lomustine/PCV is 6 weeks, while 4 weeks is clinical routine in the case of temozolomide **Continued alcohol screen only relevant if randomized to the disulfiram group. ***Blood samples as indicated here relevant as long as on active treatment and includes: hemoglobin, thrombocytes, leukocytes with differential count, ASAT, ALAT, G-GT, ALP, bilirubin, INR).

***Sample size and study power*.** The sample size calculation is based on data from previous trials reporting that 50% of patients treated with lomustine deceased within 8 months
^6^. We use a phase III end-point in a phase II setting because this study will be the basis for power calculation of a later more rigid phase III study, and because progression is less relevant in patients with already demonstrated progression/recurrence and with a short expected survival. Due to the phase II/III setting we are relaxing the alpha value to 0.10 (by convention 0.05) since phase II studies are “preliminary assessment of a new intervention before embarking on a larger and expensive randomized controlled trial”
^26^. Thus, we argue that it is good science to slightly increase the chance of false positive results (due to chance) for a relevant end-point instead of using less relevant and difficult to interpret surrogate end-points (such as progression).

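### Read literally, the follow-up stopping rule lets a control patient leave toxicity and MRI follow-up earlier than a DSF-Cu patient in the same clinical state (minor)

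*Protocol article*

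**What the plan says.** All of the following is in the protocol article.

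- **Stop rule (Data collection).** "After withdrawal of tumor target therapy no additional follow-up (including MRI) is planned within the context of this study". The reason given is to spare patients burden at the end of life. The section carries survival on to death or 24 months, and quality of life to progression, death or 24 months.
- **DSF-Cu alone (Data collection).** After progression, MRI in the DSF-Cu group may go on "as long as the patient continues on only DSF-Cu, or in combination with another established rescue therapy". The text then concludes that scans "should be continued as long as tumor targeted therapy is administered (both in control and intervention group").
- **Treatment rules (Interventions).** "The intervention should continue also after change of chemotherapy, or during temporary chemotherapy withdrawal due to reached maximal cumulative dose", or because of chemotherapy side effects. DSF-Cu is stopped permanently once tumor targeted therapy is no longer indicated. Until the study closes, "no crossover from the control group to DSF-Cu is allowed".
- **Blood tests (Participant timeline).** "hematological status and liver function will be monitored as long as patients are on active treatment". Whether DSF-Cu alone is active treatment is not stated.
- **Table 2.** Toxicity is listed at every visit to month 24. Only the blood samples carry a footnote tying them to active treatment.
- **Analysis (Statistical methods).** Safety: "Safety assessment with comparing proportion of a composite of grade 3, 4 and 5 toxicities". Fixed-time PFS: progression is assessed "by the local investigator and analyzed similar to the primary end-point", that is, with a 2x2 table and a chi-square test.

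**The concern.** When follow-up ends with therapy, and one arm has a therapy that can outlast chemotherapy and is closed to the other arm, the length of observation can depend on the arm. Harms are recorded at study visits. With equal event rates, the arm watched longer shows more patients with a grade 3-5 event, so a crude proportion would tilt against DSF-Cu. The interim safety review at 71 patients would carry the same tilt.

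For PFS at a fixed time, a patient who stops therapy unprogressed, has no further MRI and is alive at the landmark cannot be placed in a 2x2 table. Under the literal rule there could be more such patients among controls.

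This is a data collection rule. An analysis plan can shorten the window in the DSF-Cu arm, but it cannot recover control data that were never collected.

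**Working it through.** **1. The texts side by side.** The article does not define DSF-Cu as tumor targeted therapy. It lets scans continue on DSF-Cu alone and derives from this that scans last as long as tumor targeted therapy is given. That inference works only if DSF-Cu alone counts. Take two patients off chemotherapy for side effects, neither at the end of life. The DSF-Cu patient is still on such therapy and stays in. The control patient has none, cannot cross over, and under the literal rule leaves. Table 2 would keep both in toxicity follow-up, so the article contradicts itself.

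**2. Illustration of the toxicity tilt.** The article gives no toxicity rate or treatment duration, so there is no figure of its own to reproduce. Only two inputs come from it: 60% survival at 6 months and 71 patients per arm. The rest are assumptions, with no treatment effect on death or toxicity:

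- Death hazard μ = -ln(0.60)/6 = 0.0851 per month.
- Chemotherapy ends at a median of 4 months: γ = ln 2/4 = 0.1733.
- Half of patients are still indicated for therapy at that point; the other half stop in both arms.
- Of those still indicated, a share r gets rescue therapy in both arms and is followed equally. The rest leave in control and stay on DSF-Cu alone in the other arm.
- Rescue therapy or DSF-Cu alone lasts a median of 2 or 6 months: δ = 0.3466 or 0.1155.
- Grade 3-5 hazard λ corresponds to 30% or 50% by month 6 on chemotherapy (0.0594 or 0.1155), multiplied by f on DSF-Cu alone.

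Mean observation time with r = 0:

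- Control: 1/(μ+γ) = 1/0.2584 = 3.87 months.
- DSF-Cu: 3.87 + 0.5 × 0.6706 × 1/(μ+δ), which is 4.65 (δ = 0.3466) or 5.54 (δ = 0.1155). Here 0.6706 = γ/(μ+γ).
- Capping at 24 months gives 3.86 against 4.63 or 5.48.

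Excess proportion with an event on DSF-Cu = 0.5 × (1-r) × γ/(λ+μ+γ) × fλ/(fλ+μ+δ).

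- Largest (λ = 0.1155, f = 1, δ = 0.1155, r = 0): 0.5 × 0.4634 × 0.3654 = 0.085.
- Smallest with f = 0.5 (λ = 0.0594, δ = 0.3466, r = 0): 0.5 × 0.5451 × 0.0644 = 0.018.

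| Still-indicated controls on rescue | Excess, f 0.5-1.0 | Excess, f 0.25 |
|---|---|---|
| none | 1.8-8.5 points | 0.9-2.9 |
| half | 0.9-4.2 | 0.5-1.4 |
| 80% | 0.4-1.7 | 0.2-0.6 |

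The article names no test or level for safety. If a two-sided 5% chi-square test were used with 71 per arm, it would reject in 5.9-18.5%, 5.3-8.1% and 5.1-5.5% of trials in the three rows (f 0.5-1.0).

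**3. Illustration for 6-month PFS.** Assume median PFS of 2-4 months, chemotherapy ending at a median of 4-12 months, and progression hazard π = ln 2/(median PFS) - μ.

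Control share alive at month 6 with MRI stopped before progression = 0.60 × γ/(γ+π) × (1 - exp[-6(γ+π)]).

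- PFS median 4, chemotherapy end 4: 0.60 × 0.663 × 0.792 = 0.315.
- PFS median 2, chemotherapy end 12: 0.60 × 0.181 × 0.853 = 0.093.

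If deaths occur only after progression, the upper end is 0.333. If every DSF-Cu patient stays on DSF-Cu after chemotherapy and is scanned meanwhile, the DSF-Cu share is 0.020-0.199. These are upper bounds: they assume no rescue therapy and no further MRI in any unprogressed patient off therapy.

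**The case against.** The case against is substantial, and most of it stands as a limit on how often and how strongly the rule bites.

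- **Other parts of the protocol keep patients in.** Quality of life is followed to progression whatever the therapy, and in Table 2 it shares the three-monthly visit with toxicity and MRI. An unprogressed control off chemotherapy therefore has visits at which toxicity would be recorded. This stands. It makes the PFS shares ceilings and leaves a contradiction in the text, not a settled shortfall.
- **The rule is meant for the end of life, and DSF-Cu also stops when therapy is no longer indicated.** True, and at that stage both arms stop alike. But the trigger as written is withdrawal of therapy, not the change to supportive care.
- **Chemotherapy breaks are called temporary, and rescue options exist.** This stands. The gap needs a control who is still indicated, untreated and taken out of visits.
- **Toxicity during longer DSF-Cu exposure is real toxicity.** Also true, and a reason to keep those events in the comparison. The artefact is only that control events over the same calendar time go unrecorded.
- **Collection windows may be fixed in the full protocol, which is not shown.** Possible. The article nevertheless states a rule, and the rule as stated depends on arm.

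A reader might infer that the safety comparison is bound to produce false alarms. The documents do not support that: high rejection rates need windows such as 4 against 8 months, which nothing in the article suggests. A reader might also infer that scanning DSF-Cu patients after progression distorts PFS. It does not, because those scans come after the event.

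**Conclusion.** The point holds as a minor one. The stop rule, the status given to DSF-Cu alone and the crossover ban together allow the end of toxicity and MRI follow-up to depend on arm, and this conflicts with Table 2 and with the rule's own purpose. The direction is clear: against DSF-Cu for crude toxicity, and towards more unclassifiable controls for fixed-time PFS.

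The size cannot be derived from the article. It rests wholly on the assumed durations, toxicity rates and share still indicated. The tilt is probably small if most controls get rescue therapy (under 2 points at 80%), and the 8.5-point figure needs every input at its unfavourable end. The primary endpoint and overall survival are not affected, because survival is followed regardless of treatment. It would go too far to say that the trial does follow its arms unequally: sites that follow Table 2, or apply the stop only at the end of life, would not.

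**What to change.** **Amend the Data collection paragraph.** Follow-up stops in both arms only on change to supportive care alone, death or 24 months, not on withdrawal of therapy. Until then, collect toxicity and the Table 2 blood samples on the same schedule in both arms, and continue three-monthly MRI until progression.

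**Analysis.** Compare grade 3-5 toxicity over the same fixed time from randomization, for example 6 months. Estimate fixed-time PFS from the Kaplan-Meier curve instead of a 2x2 table.

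**Patients already followed under the present rule.** Cutting both arms at the end of chemotherapy or rescue therapy equalizes the window, but it conditions on a post-randomization event and drops toxicity on DSF-Cu alone. Use it only as a sensitivity analysis and report the events on DSF-Cu alone as well. With 36 of 142 patients randomized by October 2018, most could still be followed under the new rule.

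**Cost.** The amendment must go to the ethics committees and, if significant, to the two medicines agencies. Under the assumptions above, and with supportive-care patients exempt, toxicity follow-up to month 6 adds about 21-59 control and 12-26 DSF-Cu patient-months in total. Longer follow-up adds more. MRI until progression adds at most about 10-68 control scans (71 × chance that chemotherapy ends first × mean remaining PFS / 3), all on the existing schedule. Some patients off therapy bear these visits, blood samples and scans. The sample size and the primary endpoint do not change.

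### The end-point list declares PFS at 6 and 12 months, the analysis section names only 6 and 24 months, and the declared 12-month proportion has no specified comparison

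*Protocol article*

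**What the plan says.** All references are to the protocol article.

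- **Outcomes** (under Participants, interventions and outcomes) lists two PFS end-points: "Median progression free survival" and "6 and 12 month progression free survival". The primary end-point, survival at 6 months, is counted from randomisation.
- **Statistical methods** plans two PFS analyses. The first is a Kaplan-Meier plot with a log-rank test, of which it says "This analysis will also be performed at 6 months and at 24 months after the last patient inclusion". The second is the fixed-time analysis: "Actual progression free survival analyses at 6 and 24 months after the last patient inclusion". Progression for this item is assessed "by the local investigator and analyzed similar to the primary end-point".
- The primary end-point, whose method is borrowed, "will be assessed with 2x2 tables and analyzed with chi-square test". The statement that no missing data are expected is confined to the primary end-point.
- For survival, the same section uses a per-patient landmark: "Actual survival data at 24 months post-inclusion will be analyzed similar to the primary end-point".
- **Data collection** limits follow-up: "Patients will be in the trial for a maximum of 24 months or until death". Once tumour-directed therapy is withdrawn, no further MRI is planned, but survival is still followed to death or 24 months.

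**The concern.** A fixed-time proportion needs two things: the landmark, and the origin from which it is counted. For PFS the two sections disagree on the landmark (12 against 24 months), and the analysis section gives an origin, last inclusion, that is not a per-patient one. Someone writing or running the analysis cannot follow both sections.

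What is at stake is the pre-specification of one secondary end-point. Treatment is open label and progression is called locally, so it should be settled beforehand which PFS landmark beyond 6 months is compared and reported. As written, that choice could be made with the data in view.

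The second issue is the method. Vital status at 6 months should be known for nearly everyone, so a plain 2x2 table suits the primary end-point. Progression status is different, because imaging can end before progression while the patient is still alive.

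**Working it through.** **1. The texts side by side**

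| | Outcomes | Statistical methods |
|---|---|---|
| Fixed-time PFS | 6 and 12 months | 6 and 24 months |
| Origin | not restated for PFS; randomisation for survival | last patient's inclusion |
| 12-month PFS | declared | not named |
| 24-month PFS | not declared | named, as a landmark or as a cut date |

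**2. The two workable readings of the analysis item**

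- *Landmark.* Each patient is classified at 6 and at 24 months. This contradicts Outcomes, and 12-month PFS is not compared.
- *Data cut.* The analysis is run 6 and 24 months after the last inclusion. No per-patient landmark is then stated in the analysis section. At the first cut, anyone included in the preceding 6 months has between 6 and 12 months of follow-up, so a complete 12-month table is possible only at the second cut. The text does not say this.

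Neither reading yields a specified comparison of the 12-month proportion.

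**3. Patients with unknown status.** Take a patient whose tumour-directed therapy is withdrawn before documented progression and who is alive at the landmark. MRI has stopped, so progression status is unknown. A 2x2 table must either drop this patient or assign a status. Kaplan-Meier, already planned for overall PFS, censors the patient at the last assessment.

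**4. The plan's own figure.** The article gives no PFS rate. Its one calculated figure is the sample size: 60% against 80%, two-sided alpha 0.10, power 80%.

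n per arm = [1.645·√(2·0.7·0.3) + 0.842·√(0.6·0.4 + 0.8·0.2)]² / 0.2² = (1.066 + 0.532)² / 0.04 ≈ 63.9, so 64 per arm and 128 in total.

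Power at 64 per arm is 80.1%, and 128/0.9 = 142.2 agrees with the stated 142. None of this depends on PFS.

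**5. How sparse a 24-month PFS comparison would be.** Assumptions: exponential PFS with control median m, so PFS(t) = 0.5^(t/m), and 71 patients per arm. The DSF-Cu proportion is the control proportion raised to the hazard ratio (HR). Two HRs are shown: an assumed 0.70, and ln 0.8 / ln 0.6 = 0.437, which is the survival effect in the design carried over to PFS. Entries are expected numbers progression-free, of 71.

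| m (months) | Control, 12 mo | Control, 24 mo | DSF-Cu, 24 mo, HR 0.70 | DSF-Cu, 24 mo, HR 0.437 |
|---|---|---|---|---|
| 2 | 1.1 | 0.0 | 0.2 | 1.9 |
| 3 | 4.4 | 0.3 | 1.5 | 6.3 |
| 4 | 8.9 | 1.1 | 3.9 | 11.5 |
| 6 | 17.8 | 4.4 | 10.2 | 21.1 |

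Exact power of the uncorrected chi-square test at 24 months (two-sided alpha 0.10), for m = 2, 3, 4 and 6:

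- HR 0.70: 0.1%, 14%, 39% and 49%.
- HR 0.437: 29%, 90%, 97% and 99%.

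A ceiling for the control arm follows from the 8-month median survival under Sample size and study power, because PFS cannot exceed survival. If survival is exponential, 0.5^(24/8) = 0.125, and 0.125 × 71 ≈ 9 patients.

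**The case against.** The strongest reply is that the phrase about last inclusion is a run date and nothing more. Statistical methods uses it that way for the primary end-point, which is defined per patient, and for the overall survival and PFS curves. The 24-month limit on follow-up supports this: status 24 months after the last inclusion could not be collected for patients included earlier. Outcomes would then supply the landmarks, and both could be tabulated at the later cut. This reading is plausible and may be the intended one. It does not settle the matter, because the analysis item still names no landmark and never mentions 12 months.

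Two stronger conclusions are tempting, and the article supports neither.

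- A reader might infer that 12-month PFS has been replaced by an almost empty 24-month table. Replacement holds only on the landmark reading. Emptiness needs PFS rates that the article does not give, and in both arms together it needs a median of about 3 months or less with a moderate or no effect. With the design-size effect, about 2 to 12 of 71 on DSF-Cu would be progression-free at 24 months for control medians of 2 to 4 months.
- A reader might add that dating from last inclusion gives patients unequal follow-up within one table. That cannot be charged together with an empty 24-month landmark: a per-patient landmark gives equal follow-up, and a calendar status date is not 24-month PFS. The use of the phrase elsewhere in the section points away from a calendar status date.

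It is also fair to say that PFS around 12 months is not left unanalysed, since the Kaplan-Meier curve gives a 12-month estimate and the log-rank test uses the events up to then. Neither is a specified comparison of the 12-month proportion. Finally, rules for unknown progression status are often left to an analysis plan, which is not shown here. But the article itself fixes the 2x2 chi-square for PFS, and that choice has no room for such patients.

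**Conclusion.** The point holds as an inconsistency between the declared end-point and its analysis, and this needs no assumed figures. No comparison of the 12-month PFS proportion is specified on either reading, and the 2x2 method does not suit an outcome whose status can be unknown.

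Its reach is limited to one secondary end-point. The 6-month landmark appears in both sections, so the ambiguity concerns only the second one. The primary end-point, alpha and sample size are untouched.

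The sparseness of a 24-month comparison is a conditional remark about the control arm only: about 0 to 1 of 71 for assumed medians of 2 to 4 months, and at most about 9 of 71 if survival is exponential with the article's 8-month median. It should be corrected, but it does not threaten the trial's main conclusion.

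**What to change.** In Statistical methods, replace the item on actual PFS with: PFS at 6 and 12 months after each patient's randomisation, estimated by Kaplan-Meier, with the between-arm difference and its confidence interval.

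Give the data cuts (6 and 24 months after last inclusion) in a separate sentence. Say that 12-month PFS is reported at a cut when all patients have 12 months of follow-up, which of the two planned cuts is the later one.

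If a 24-month PFS comparison is also wanted, declare it in Outcomes and note that the control arm is likely to be sparse.

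The cost is wording only. No extra patients, visits or data are needed, and Kaplan-Meier estimation of PFS is already planned.

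### Screening EQ-5D is collected but has no prespecified role in the cumulative quality-of-life comparison, which gives up some precision and leaves any baseline adjustment to a post-hoc choice

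*Protocol article*

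**What the plan says.** Health-related quality of life is a declared secondary end-point (protocol article, Outcomes).

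- **Collection.** The EQ-5D row of Table 2 reads "Euroqol-5D 3L X X": one mark under screening (month 0) and one under the three-monthly visits. The Data collection paragraph ends this follow-up early: "Quality of life will be monitored until progression, death or 24 months post-inclusion".
- **Analysis.** The Statistical methods paragraph plans a "Comparison of general health related quality of life at 6 and 24 months after last included patients" and continues "We will use an area under the curve approach (i.e. cumulative quality of life"). It names no test, model or covariate for this outcome. It does not say whether the screening value is the first point of the curve.
- **Adjustment.** The last paragraph of Statistical methods begins "We stratify only for study center, however important baseline variables like repeated surgery, time since primary treatment, age, functional status", goes on to chemotherapy type and biomarkers, and says that these "will be registered and adjusted for in post-hoc exploratory analyses". Functional status is listed; baseline EQ-5D is not. The word 'like' makes the list open.
- **Design.** Randomization is stratified by centre only.

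**The concern.** The baseline measurement of an outcome is usually among its best predictors. Here it is taken before treatment starts, so it can serve as a covariate without being affected by the arm. If it is left out, the variation between patients that it explains stays in the error term, and the confidence interval is wider than it needs to be.

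The second issue is discretion. Nothing in the design balances quality of life at entry. If the arms happen to differ at screening, the plan as written allows adjustment only after the fact. In an open-label trial of an add-on drug, where readers will ask whether the drug costs quality of life, an adjustment chosen once the results are known is hard to defend.

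**Working it through.** **The plan's own figures.** The article gives no figure for the quality-of-life comparison. Its sample size reproduces: for 60% versus 80%, two-sided alpha 0.10 and power 80%, n per arm = [1.645·√(2·0.7·0.3) + 0.842·√(0.24+0.16)]² / 0.20² = 63.9, so 64 per arm and 128 in total. Then 128/0.9 = 142.2, given as 142 (71 per arm). None of this depends on the present point.

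**Formula.** Let r be the correlation between screening EQ-5D and the AUC. The ratio of the adjusted to the unadjusted standard error is √(1 − r²). The documents give no r, so it has to be built from assumptions.

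**Step 1: complete follow-up (an upper bound).** Assume a trapezoid curve that starts at screening and an equal correlation c between any two visits. For 0, 3 and 6 months the weights are 0.25, 0.50 and 0.25. With c = 0.5:
- covariance with baseline = 0.25 + 0.5·0.75 = 0.625
- variance = 0.375 + 0.5·0.625 = 0.6875
- r² = 0.625²/0.6875 = 0.568, so the ratio is √0.432 = 0.657

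For c = 0.3, 0.5 and 0.7 the standard error falls by 23%, 34% and 49% (6 months) and by 17%, 30% and 45% (24 months). These figures should not be relied on, because monitoring stops at progression or death and the plan itself expects 40% of controls to be dead by 6 months.

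**Step 2: curve ends at progression or death.** This was simulated with 200,000 patients per scenario. Assumptions: EQ-5D mean 0.65 and SD 0.25, limited to −0.2 to 1; c = 0.3, 0.5 or 0.7; exponential event time with median 2, 4 or 8 months; the last value carried to the event within an interval; baseline EQ-5D either unrelated to event time or lengthening it by a factor exp(0.2) per SD.

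| Horizon | Smallest gain | Median 4 months, c = 0.5, no link | Largest gain |
|---|---|---|---|
| 6 months | ratio 0.960 (4%) | 0.929 (7%) | 0.809 (19%) |
| 24 months | ratio 0.985 (2%) | 0.976 (2%) | 0.907 (9%) |

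The gain is smaller than in Step 1 because the length of follow-up alone explains about 58-90% of the AUC variance, and screening EQ-5D says little about length.

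A different rule, with deaths scored 0 and 60% alive at 6 months, gave r of 0.36 to 0.52. The ratios are √(1 − 0.36²) = 0.933 and √(1 − 0.52²) = 0.854, a cut of 7-15%, which lies inside the 6-month range.

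**Step 3: what this is worth.**
- Equivalent patients per arm, 71/ratio²: at 6 months 71/0.960² = 77 to 71/0.809² = 108; at 24 months 71/0.985² = 73 to 71/0.907² = 86.
- Power, for an effect detectable with 80% power unadjusted (alpha 0.10 borrowed from the primary end-point), is Φ[(1.645 + 0.842)/ratio − 1.645]: about 83% to 92% at 6 months and 81% to 86% at 24 months.

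**The case against.** The strongest case against is that this is analysis-plan detail. The article condenses protocol version 2.0, no analysis plan is shown, and the covariates of one secondary outcome are usually settled there. A reader might infer that the screening EQ-5D will be ignored and adjusted for nowhere. The text does not support that: it names no model for this outcome, and the list of baseline variables is open. That the curve starts at screening is the usual construction, but it is not written either. What remains is that the article is not merely silent. It states where baseline adjustment belongs, namely in post-hoc exploratory analyses, and an analysis plan with screening EQ-5D in the main model would depart from that statement.

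A reader might also infer bias, or a spurious effect. With an assumed SD of 0.25, the standard error of a chance baseline difference is 0.25·√(2/71) = 0.042. If it persisted in full for half a year, that would be 0.042·0.5 = 0.021 quality-adjusted years. Full persistence is not credible: with c = 0.5 and complete follow-up, 0.625 of the difference carries over, giving 0.042·0.625·0.5 = 0.013, and stopping at progression or death would be expected to reduce it further. In any case this is ordinary sampling error under randomization, already covered by the unadjusted standard error. The unadjusted test stays valid.

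The objection that the AUC may be far from normal when follow-up is cut short also stands. It bears on how the regression is done, not on whether the covariate is used.

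**Conclusion.** The point holds as a low-cost improvement to one secondary end-point. The screening EQ-5D is collected, the AUC comparison gives it no prespecified role, and the stated policy makes baseline adjustment post hoc. The loss is one of precision and of protection against a data-driven choice of adjustment; validity is not at stake. The gain is modest: about 4-19% off the standard error at 6 months and 2-9% at 24 months. These ranges rest entirely on the assumed SD, visit correlations and event times, and on a curve that starts at screening and stops at progression or death.

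**What to change.** Add one sentence on quality of life to Statistical methods, and carry it into the analysis plan before any outcome is compared by arm. Suggested text: *The EQ-5D area under the curve, starting at the screening value, will be compared between arms by regression on treatment arm with screening EQ-5D as covariate; the adjusted difference and its confidence interval will be reported, with the unadjusted comparison beside it.*

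Centre, as the stratification factor, may be added. If the AUC is skewed, use robust or bootstrap standard errors. The last paragraph of Statistical methods should then exempt this covariate from the post-hoc rule.

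The cost is one degree of freedom, plus seven if all eight centres enter as separate terms. No new data, visits or patients are needed.
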